### Study objectives and outcome measures

The primary study objectives are:To evaluate the effectivity of vaginal application of imiquimod 5% in the treatment of recurrent or persistent CIN. The primary outcome measure is reduction to normal cytology of the cervix at 26 weeks after start treatment in imiquimod and LLETZ group.

Secondary study objectives and outcome measures are:To evaluate the effectivity of vaginal application of imiquimod 5% in the treatment of recurrent/residual CIN; reduction to absence of dysplasia in histology at 26 weeks as compared to baseline in the Imiquimod group.Evaluate of the effect of treatment on HPV DNA positivity of CIN lesions, by comparison of PCR HPV-DNA detection at cervical biopsies/cytology taken at 0 and 26 weeks.Establish the incidence and severity of side effects of LLETZ and imiquimod therapy.Review the Quality of life (QoL) in patients at 0 and 20 weeks and after 1 year by the following QoL questionnaires: RAND 36, QLQ-C30 and QLQ-CX24.Estimate the long term recurrence rate of CIN lesions measured by reduction to PAP1 by cytology examination at 6, 12 and 24 months after treatment. We will request the first outcome taken by the Dutch screening program for cervical cancer: cytology or HPV status will be obtained.

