### Sample size calculation

The regression rate of a second LLETZ procedure is estimated 63% in a retrospective cohort (data not published). The regression rate of CIN lesions after treatment with imiquimod was based upon the only study reporting on the regression rate after 16 weeks of imiquimod therapy of primary CIN. This study showed a regression rate of 73% in patients with primary CIN lesions [23]. Since the effect could be lower in patients with residual or persistent CIN, we estimated the regression rate to be 60%.

To calculate the required sample size in this two-proportions non-inferiority trial we assume that the probability of regression is 63% for the standard (LLETZ procedure) while it is 60% after treatment with imiquimod.

Using a non-inferiority margin of 10% for the difference in proportions and a significance level (alpha) of 5%, a sample size of 174 per group is required to obtain a power of at least 80%. Allowing for 20% loss to follow-up the total required sample size is 433.

Because the uncertainty in the assumptions an interim analysis for futility will be performed by the Data Monitoring Committee (DMC) as soon as the primary outcome is available for 35 patients. This interim analysis is based on predictive power. That is the predicted probability of being able to prove non-inferiority given the results at the interim analysis. When the predictive power at this point is below 20% the trial will be stopped due to futility. Of course the DMC can always stop the trial due to safety concerns. The trial will never be stopped prematurely for efficacy so no alpha-adjustment is made.

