### Statistical methods

Analysis will be done according to the intention to treat principle and the non-inferiority principle to show that imiquimod is not worse than an existing treatment (LLETZ). To investigate efficacy we will perform a per protocol analysis (although this is not the primary outcome of the study). The primary outcome is the difference between the probability of regression in the LLETZ and the imiquimod arms. The expected difference (LLETZ-imiquimod) will be calculated together with the 95% Aggresti confidence interval. If the upper bound of the interval lies below the non-inferiority margin of 10% non-inferiority of the imiquimod treatment is assumed to be proved. Logistic analysis of potential confounders (age at diagnosis, CIN grade, number of previous treatments, smoking, HPV-subtype) will be performed. Analysis will be based on intention to treat protocol.

The prevalence and severity of side effects of imiquimod and LLETZ treatment, as documented according to Common Terminology Criteria for Adverse Events guidelines, will be presented as proportions and means with 95% confidence intervals. Differences in the rates of overall side-effects and severe side-effects between the imiquimod and LLETZ groups will be tested with a chi-square test. Disease recurrence rates, defined by abnormal cervical cytology, after 6, 12 and 24 months will be evaluated in adequately treated patients by use of multiple logistic regression analysis, after adjustment for age at diagnosis, CIN grade, smoking sexual behavior and HPV subtype.

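### Side-effect severity is to be summarised by unnamed means, most naturally mean CTCAE grade; counts by worst grade and risk differences would serve better

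*Protocol article*

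**What the plan says.** The secondary objective (protocol article, Study objectives and outcome measures) is to "Establish the incidence and severity of side effects of LLETZ and imiquimod therapy".

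Statistical methods names the quantities as "The prevalence and severity of side effects of imiquimod and LLETZ treatment", "as documented according to Common Terminology Criteria for Adverse Events guidelines", and says that they "will be presented as proportions and means with 95% confidence intervals". It does not say which measure goes with prevalence and which with severity, or what the means are means of.

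The next sentence gives the comparison of the arms: "Differences in the rates of overall side-effects and severe side-effects between the imiquimod and LLETZ groups will be tested with a chi-square test". It names a test and no interval for the difference.

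The Data collection subsections list adverse effects of imiquimod at 6, 10, 16 and 26 weeks, both reported by patients and seen at clinical investigation. For LLETZ they list adverse effects at 6 weeks only, reported by patients.

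**The concern.** Two things are paired with two summaries. Taken in order, prevalence gets proportions and severity gets means. CTCAE grade is the only severity measure that the article names, so the likely figure is a mean grade with a 95% interval. A mean of grades counts one grade 3 event the same as three grade 1 events, and neither the mean nor its interval corresponds to a number of patients harmed.

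The treatments differ in a way that brings this out. The cream is applied three times a week for 16 weeks, with local and mild systemic effects foreseen (Interventions). A single excision carries risks such as haemorrhage and infection (Abstract). Many low grades in one arm and a few high grades in the other is the pattern that a mean describes worst.

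The terms also differ: the objective is incidence, while the analysis is of prevalence. With repeated visits these are different quantities. What is at stake is how clearly a secondary safety table can be read. The primary analysis is not involved.

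**Working it through.** The article gives no side-effect rate, mean grade or standard deviation, so there is no planned figure to reproduce. The check is whether a mean grade can mislead, and whether the rest of the plan would reveal it.

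**Inputs.** 174 patients per arm (Sample size calculation), used only for scale. All grade distributions are assumed. It is also assumed that CTCAE grades are ordered categories, and that severe means grade 3 or higher; the article states neither.

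**Illustration A, assumed percentages.** Imiquimod: 60% grade 1, 10% grade 2, the rest unaffected. LLETZ: 20% grade 1, 12% grade 3, the rest unaffected.

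- Mean with unaffected patients as grade 0: imiquimod 0.60×1 + 0.10×2 = 0.80; LLETZ 0.20×1 + 0.12×3 = 0.56.
- SD: imiquimod √(0.60×1 + 0.10×4 − 0.80²) = 0.60; LLETZ √(0.20×1 + 0.12×9 − 0.56²) = 0.98.
- 95% interval, mean ± 1.96×SD/√174: imiquimod 0.71 to 0.89; LLETZ 0.41 to 0.71.
- Mean among affected patients: imiquimod 0.80/0.70 = 1.14; LLETZ 0.56/0.32 = 1.75.
- Severe: 0% against 12%.

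**Illustration B, assumed counts, with some severe events in both arms.**

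| | Imiquimod | LLETZ |
|---|---|---|
| Patients at grade 0/1/2/3 | 26/87/57/4 | 122/26/9/17 |
| Mean, unaffected as 0 | 213/174 = 1.22 (1.12 to 1.33) | 95/174 = 0.55 (0.40 to 0.69) |
| Mean, affected only | 213/148 = 1.44 | 95/52 = 1.83 |
| Grade 3 or higher | 4/174 = 2.3% | 17/174 = 9.8% |

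In both illustrations the mean over all patients puts imiquimod as worse, while the mean over affected patients and the severe rate put LLETZ as worse. The order depends on a denominator that the article does not state.

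**Equal means.** All patients at grade 2, or half at grade 1 and half at grade 3, both give 2.0, with 0% and 50% severe.

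**Does the rest of the plan reveal it?** Yes. In B the planned chi-square test on severe side effects (uncorrected) gives 8.56, p = 0.003. In A, 0 against about 21 patients (0.12×174 = 20.9) would be plain. What the test does not give is the size of the difference. In B that is 13/174 = 7.5 percentage points, with standard error √[(0.023×0.977 + 0.098×0.902)/174] = 0.025 and a simple 95% interval of about 2.5 to 12.4 points.

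**Incidence and prevalence.** Suppose a side effect is present in 20% of patients at each of the three visits at weeks 6, 10 and 16. If the same patients are affected each time, 20% were ever affected. If different patients are affected each time, it is 3×20% = 60%.

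**The case against.** The article never says that CTCAE grades will be averaged. Severity as proportions by grade, or a mean number of side effects per patient, also fits the sentence, and a condensed article may leave table layout to a fuller document. This stands in part: the mean grade is an inference. But the summary is stated, and every reading leaves the averaged quantity unnamed, so the sentence needs the same edit.

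A reader might infer that the harm side of a non-inferiority result would rest on a misleading mean. The documents do not support that. The next sentence compares the arms on overall and severe rates, and no test or decision uses a mean. The article's argument for avoiding repeat excision also rests largely on reproductive and long-term outcomes (Background). This objection stands in full.

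A reader might also infer that the mean will rank the arms wrongly. That does not follow either. The reversal comes from assumed rates and from counting unaffected patients as grade 0; among affected patients it disappears in both illustrations. What stands is that the order can depend on an unstated choice.

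The mismatch of terms is real, but the test itself speaks of rates, and the 20% to 60% range is hypothetical. An interval for the between-arm difference is an improvement, and its absence from the article is not an error.

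Finally, a worst-grade table is not free of bias. Imiquimod has four listed assessments and LLETZ one, so a maximum over the whole period would favour LLETZ through ascertainment alone. This stands and shapes the fix.

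**Conclusion.** The point holds as a minor improvement to a secondary, descriptive summary. On its natural reading the sentence fixes a mean of an ordered grade, whose value and even direction can depend on an unstated denominator (0.80 v 0.56 or 1.14 v 1.75 in illustration A). Objective and analysis also name different quantities. The planned comparison of severe rates protects the conclusion on severe events, so the mean would mislead beside that comparison without driving it. All rates used are assumptions; the documents support no estimate of how likely a reversal is. Sample size, alpha and the primary analysis are unaffected.

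**What to change.** In Statistical methods:

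1. Drop the means. Report the number and percentage of patients by worst CTCAE grade and arm, with the time window stated and a note of which grades count as severe.
2. Call this incidence, to match the objective.
3. Beside the chi-square tests, give the between-arm risk difference with a 95% interval for any and for severe side effects. The interval method of the primary outcome can be reused.
4. Make the between-arm comparison over the shared window up to week 6. Show imiquimod data from weeks 10, 16 and 26 descriptively and label them as having no LLETZ counterpart.

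The cost is wording and one longer table; CTCAE documentation is already planned, and no visits or patients are added. There are two limits to state with the results. The shared window covers only 6 of the 16 weeks of imiquimod, so the comparison does not capture its later side effects. Even at week 6 the imiquimod arm also has findings from clinical investigation, so patient-reported effects are the like-for-like part.

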### Interventions

Patients will receive verbal and written information about the study procedure. They have to sign an informed consent, where after patients are randomized into the intervention arm or the standard treatment:Intervention arm: Imiquimod treatment. Patients in this group have to insert imiquimod 5% cream intravaginally for 16 weeks.Standard treatment. A LLETZ procedure is performed according to the current guidelines.

Patients in the imiquimod treatment group will apply imiquimod 5% cream intravaginally during 16 weeks. One sachet contains 12,5 mg of imiquimod and is applied with a vaginal applicator. The application frequency is 3 times a week. Patients get instructions and administer the cream themselves, before bedtime. The patients are advised to take an intravaginal shower with an applicator the next morning in order to remove cream leftovers, followed by an external shower to remove any remains on the vulva. Anti-inflammatory drugs (paracetamol or NSAID) can be used in case of mild systemic drug-related side effects. If the local or systemic side effects persist or are severe, patients are advised to reduce the frequency of the imiquimod insertion, first twice weekly, subsequently once weekly. Imiquimod treatment is discontinued for maximum of a week in case of persistent side effects. In order to prevent pregnancy, patients are advised to use adequate contraception. Subjects should refrain from vaginal sexual intercourse during the nights that imiquimod is applied until the vaginal shower the next morning. After 10 weeks a colposcopy is performed to rule out disease progression. Biopsies are only performed in case of suspicion of invasive disease.

In the standard treatment group, patients will undergo a LLETZ procedure within 4 weeks after the diagnosis. Excision of macroscopic lesions and the transformation zone will be achieved by a monopolar loop electrode, preferably under local anaesthesia.

Treatment efficacy is evaluated at 26 weeks follow-up for both groups. The Imiquimod group will have a Pap smear and a colposcopy with diagnostic biopsies. Biopsies are performed at the initial CIN lesion site and at any other suspect site, with a minimum of two. In case of persistent or progressive disease, surgical excision is performed. The LLETZ group will have follow-up with cervical smears at 6, 12 and 24 months according to the current guidelines.

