#### 6 weeks follow-up

Adverse effects of imiquimod treatment: patient reported side effects and side effects noticed at clinical investigation.Adverse effects of LLETZ treatment: patient reported side effects.

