#### 10 weeks follow-up

Treatment compliance: amount of applied doses of imiquimod for the imiquimod group.Adverse effects of imiquimod treatment: patients reported side effects and side effects noticed at clinical investigation.Colposcopy with biopsies to determine progressive or invasive disease in the imiquimod group.

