#### 16 weeks follow-up

Adverse effects of imiquimod treatment: patient reported side effects and side effects noticed at clinical investigation.

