#### 12 and 24 months follow-up

Cervical cytology outcomes for all treatment groups, including HPV genotyping.

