### Ethical considerations and dissemination

The standards outlined in the Declaration of Helsinki are guidelines for the study. Before the start of the study there was approval of the ethics committee. There is a data management safety board throughout the study. We will record adverse events and reported them to local protocol. We will be offering the study results for publication in international medical journals. If the subject agreed on this, study results will be communicated to trial participants by mail.

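### The chi-square test of side-effect rates partly reflects unequal scheduled assessment: four visits with clinical examination on imiquimod, one patient report after LLETZ

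*Protocol article*

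**What the plan says.** Side effects are a secondary objective for both treatments: "Establish the incidence and severity of side effects of LLETZ and imiquimod therapy" (Study objectives and outcome measures). Under Statistical methods they are to be graded by the Common Terminology Criteria for Adverse Events (CTCAE) and presented as proportions and means with 95% confidence intervals. They are then compared formally: "Differences in the rates of overall side-effects and severe side-effects between the imiquimod and LLETZ groups will be tested with a chi-square test". No common visit, time window or mode of detection is named for that test.

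The Data collection section lists side effects differently by arm:

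- At 6 weeks, imiquimod side effects come from patient report and clinical investigation. The LLETZ entry is "Adverse effects of LLETZ treatment: patient reported side effects".
- At 10 weeks, for imiquimod only: "Adverse effects of imiquimod treatment: patients reported side effects and side effects noticed at clinical investigation".
- At 16 weeks, for imiquimod only: "Adverse effects of imiquimod treatment: patient reported side effects and side effects noticed at clinical investigation".
- At 26 weeks, the imiquimod list repeats the item with both sources. The LLETZ list has cytology, HPV genotype, quality of life and, after an abnormal smear, the grade of dysplasia. It has no side-effect item.
- At 12 and 24 months, for both arms: "Cervical cytology outcomes for all treatment groups, including HPV genotyping".

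Separately, Ethical considerations and dissemination says: "We will record adverse events and reported them to local protocol".

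**The concern.** A chi-square comparison of two proportions is interpretable as a treatment effect only if an event of the same kind has a similar chance of being recorded in either arm. Here three features differ by design, and all point the same way: imiquimod patients are asked more often, over a longer period, and are also examined. LLETZ effects that arise after week 6, or that show only on examination, have no scheduled route into the comparison.

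The trial's rationale is to spare women the complications of a repeat excision, and the Discussion links the clinical applicability of imiquimod to the documentation of side effects. A comparison tilted against imiquimod could distort that judgement. The problem lies in what is collected as well as in how it is analysed: an analysis plan can narrow the test, but it cannot recover LLETZ answers at 26 weeks that nobody asked for.

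**Working it through.** **Step 1. Count the scheduled side-effect assessments** (Data collection).

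| Time | Imiquimod | LLETZ |
|---|---|---|
| 6 weeks | report + examination | report |
| 10 weeks | report + examination | none |
| 16 weeks | report + examination | none |
| 26 weeks | report + examination | none listed, though the visit exists |
| 12, 24 months | none | none |

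The count is four against one. The only item with the same time and source in both arms is the patient report at 6 weeks.

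**Step 2. Inputs.** The article gives no expected side-effect rate and no power for this test, so there is no plan figure to reproduce. I take n = 174 per group from Sample size calculation as given. Whether that number follows from its own assumptions is a separate question. The per-assessment probability q, the correlation between visits and the sensitivity of patient report are not in the documents. All three are assumptions, shown as ranges.

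**Step 3. Frequency alone, independent visits.** Give each assessment in either arm the same probability q of recording a side effect. LLETZ then shows q and imiquimod shows 1 − (1 − q)^4. The chance that a two-sided 5% test rejects is Φ[(d − 1.96·SE0)/SE1]. Here d is the difference in proportions, SE0 = √(p̄(1 − p̄)·2/n), p̄ is the mean of the two proportions, and SE1 = √((p1(1 − p1) + p2(1 − p2))/n).

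Example, q = 10%:
- p1 = 0.100 and p2 = 1 − 0.9^4 = 0.344, so d = 0.244 and p̄ = 0.222.
- SE0 = √(0.222 × 0.778 × 2/174) = 0.0446.
- SE1 = √((0.090 + 0.226)/174) = 0.0426.
- (0.244 − 0.087)/0.0426 ≈ 3.7, so the test rejects in over 99% of trials.

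| q | LLETZ | Imiquimod | Rejection |
|---|---|---|---|
| 2% | 2.0% | 7.8% | about 70% |
| 5% | 5.0% | 18.5% | about 98% |
| 10% | 10.0% | 34.4% | over 99% |
| 20% | 20.0% | 59.0% | over 99% |

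**Step 4. Correlated visits.** A patient who reports a side effect at one visit is likely to report it again. If the four imiquimod visits carry the information of only two independent ones, imiquimod shows 1 − (1 − q)². The rejection rate is then about 40% at q = 5% (9.8% against 5%), 67% at q = 10% (19% against 10%) and 92% at q = 20% (36% against 20%). If all four visits capture the same event, the number of visits adds nothing.

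**Step 5. Mode of detection alone.** Suppose visits are fully correlated, the true rate is p in both arms, and patient report alone catches a share s of what report plus examination catches. The test then compares p·s (LLETZ) with p (imiquimod).

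| True rate p | Rejection, s = 80% | Rejection, s = 60% |
|---|---|---|
| 10% | about 10% | 28% |
| 20% | 16% | 53% |
| 30% | 24% | 75% |

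**Step 6. Common assessment.** If both arms are compared on one shared assessment with the same source, equal rates give equal expected proportions and the nominal 5%.

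**The case against.** The strongest reply is that Step 3 confuses exposure with ascertainment. The article states: "Patients in the imiquimod treatment group will apply imiquimod 5% cream intravaginally during 16 weeks". LLETZ is a single procedure. If weeks 10 and 16 reveal new side effects during continuing treatment, imiquimod's cumulative incidence really is higher, and the gap is not an artefact. It would be pure artefact only if LLETZ patients had the same continuing rate after week 6, unobserved, and nothing in the documents supports that. The model also keeps the full rate at week 26, ten weeks after the cream is stopped. This stands: the Step 3 figures illustrate an upper case and do not estimate the bias. A reader might infer from 59% against 20% that the test would be highly significant with no true difference. The documents give neither the per-visit rate nor the independence that this reading needs.

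It can also be said that adverse events are recorded generally, that side effects of both treatments are to be CTCAE graded, that a safety board exists, and that the full protocol behind this article is not shown. So a reader who infers that LLETZ complications after week 6 will be missed goes too far; they may well be recorded. But the general sentence sets no schedule or source by arm and does not equalise the itemised lists.

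More visits during a 16-week self-applied treatment are reasonable for monitoring. That explains weeks 10 and 16. It does not explain why the side-effect item is absent for LLETZ at 26 weeks, when both arms are evaluated and both report quality of life.

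Finally, this is a secondary outcome, the non-inferiority conclusion does not rest on it, and the tilt runs against the new treatment. All true, and it limits the weight of the point.

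**Conclusion.** The point holds in a limited form. As written, the between-arm test of overall and severe side effects combines any real treatment difference with unequal frequency, duration and mode of detection, and these data cannot separate them. The tendency is to overstate imiquimod's side-effect rate relative to LLETZ. A reader might go further and say that the test merely measures how often patients were asked. The documents do not support that, because the test would also respond to real differences between 16 weeks of cream and one excision.

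The size cannot be fixed from the documents. With 174 per arm and equal assumed underlying rates, the rejection rate ranges from about 10% (fully correlated visits, patient report 80% sensitive, true rate 10%) to over 99% (independent visits, 10% or more per assessment), against a nominal 5%. If visits were fully correlated and patient report caught everything that examination does, there would be no inflation. The finding calls for a correction to a secondary comparison and does not threaten the primary analysis.

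**What to change.** 1. Add a patient-reported side-effect question, CTCAE graded, to the existing 26-week LLETZ visit. Use the same wording in both arms, covering the period since the previous shared assessment at week 6.
2. Base the formal chi-square tests of overall and severe side effects on patient reports from the visits that both arms share, 6 and 26 weeks, which together cover weeks 0 to 26.
3. Report the imiquimod data from weeks 10 and 16, and all findings at clinical investigation, descriptively by visit beside the tests.

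The practical cost is one e-CRF item at a visit that already takes place, plus a change of analysis wording. There is also a statistical cost. Recall at 26 weeks spans 20 weeks (26 − 6), and the formal test leaves out effects reported only at weeks 10 and 16. It may therefore understate transient imiquimod effects, so the by-visit description has to be shown with it. Testing at week 6 alone would be worse on this count, since it would leave ten of the 16 treatment weeks (16 − 6) out of the comparison. The change removes most of the imbalance but not all: imiquimod patients are still seen and questioned in between, which may sharpen their recall.

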Apart from reproductive arguments there is an ongoing debate on the long-term outcome after treatment with surgical excision. Several studies show a recurrence rate of CIN 2–3 after treatment of 15–22% within 2 years [15]. Margin involvement seemed to be a risk factor for developing residual or recurrent cervical dysplasia [15]. Moreover, even after adequate treatment and follow up with normal smear results, patients who were treated for cervical intraepithelial dysplasia seem to have an excessive risk of cervical cancer compared to patients with normal primary smear test results [16, 17]. This risk is even almost 25 times higher in patients with abnormal smear test results than in patients with normal smear test results after treatment [18]. Recent studies found that most women with residual or recurrent disease test positive for HPV after treatment [19, 20]. Possibly this could be a tool for risk stratification in the follow up after treatment. Moreover, treatment failure could be related to the HPV status. This could raise the question if patients of this specific group could benefit from a non-invasive treatment modality to treat HPV and avoid further surgical treatment.

A potential agent in non-invasive therapy is imiquimod cream. Imiquimod 5% cream is a topical immune response modifier with indirect antiviral and antitumor properties. It is prescribed for HPV-associated genital warts, superficial basal cell carcinoma and actinic keratosis. Studies showed that it is a safe and effective treatment for usual type vulvar intraepithelial neoplasia (VIN), which is pathophysiologically comparable to CIN [21]. Furthermore, imiquimod seems also to be effective in primary CIN lesions [22]. It would also be helpful to determine a model to predict the responders to imiquimod therapy. This could select patients for non-ablative treatment.

The Topic 2 trial is a single blinded, randomized controlled trial with two intervention arms, in which imiquimod treatment is compared to standard treatment by LLETZ in patients with residual/recurrent CIN lesions after previous ablative treatment. The aim of the study is to investigate whether topical applied imiquimod is effective in the treatment of residual and recurrent CIN lesions.

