## Methods

### Setting and study population

Patients are recruited at the moment in the Erasmus Medical Center, Rotterdam and in the Meander Hospital, Amersfoort, The Netherlands. This takes place at the outpatient clinic of gynecology. When non futility is proven after the pilot study, we intend to carry out a multi-center trial in the future throughout the Netherlands. Patients can be included if they have histologically confirmed residual or recurrent CIN lesions (CIN 1–3) after previous ablative treatment at least 6 months before the current diagnosis and have an age above 18 years. They are excluded if they have adenocarcinoma in situ, a history of (micro-) invasive cancer, hypersensitivity to the substance, immunodeficiency, pregnancy or lactation and insufficient knowledge of the English or Dutch language.

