### Randomization

Randomization is performed by use of a computerized randomization tool, to prevent selection and allocation bias.

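### The recurrence model omits number of previous treatments, a confounder the plan names for regression, in a subset where randomisation no longer guarantees balance on it

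*Protocol article*

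**What the plan says.** Both lists stand in Statistical methods in the protocol article. After the primary non-inferiority comparison, the section says: "Logistic analysis of potential confounders (age at diagnosis, CIN grade, number of previous treatments, smoking, HPV-subtype) will be performed". The next paragraph turns to recurrence at 6, 12 and 24 months, meaning abnormal cytology at those visits. The analysis set and method are given as: "will be evaluated in adequately treated patients by use of multiple logistic regression analysis". The covariates of that model then follow: "after adjustment for age at diagnosis, CIN grade, smoking sexual behavior and HPV subtype". The second list drops number of previous treatments and adds sexual behaviour. No reason is given for either change, and no other section restores the dropped term.

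The recurrence objective is secondary. Study objectives and outcome measures words it as: "Estimate the long term recurrence rate of CIN lesions measured by reduction to PAP1 by cytology examination at 6, 12 and 24 months after treatment". Eligibility requires "histologically confirmed residual or recurrent CIN lesions (CIN 1–3) after previous ablative treatment at least 6 months before the current diagnosis", with no limit on how many earlier treatments a patient may have had, so the count can vary between patients.

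**The concern.** Among all randomised patients, allocation protects a comparison of arms from systematic imbalance in treatment history. The recurrence model does not use all randomised patients. It uses those regarded as adequately treated, a status known only after allocation and reached by different routes in the two arms. Imiquimod is 16 weeks of self-application with possible frequency reduction and interruption; LLETZ is a procedure. If patients with more earlier treatments are less likely to enter the subset in one arm than in the other, the two subsets differ in treatment history. If that history also predicts recurrence, part of the difference is credited to treatment.

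The plan already regards this factor as a potential confounder for a closely related measurement. The primary outcome is normal cytology at 26 weeks, and the first recurrence time point is cytology at 6 months. At stake is how the secondary recurrence results are read.

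**Working it through.** **1. The two lists side by side (Statistical methods).**

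| Covariate | Regression analysis | Recurrence model |
|---|---|---|
| Age at diagnosis | yes | yes |
| CIN grade | yes | yes |
| Number of previous treatments | yes | **no** |
| Smoking | yes | yes |
| HPV subtype | yes | yes |
| Sexual behaviour | no | yes |

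The plan states no figure that depends on this choice, so there is none to reproduce.

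**2. Size of the possible bias (illustration).** Inputs assumed, not from the protocol: 30% of patients have more previous treatments; recurrence is about 18%; the true arm odds ratio is 1; 63% (LLETZ) and 60% (imiquimod) of patients enter the subset. The last pair borrows the regression rates in Sample size calculation as stand-ins.

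Let *a* be the factor by which more previous treatments lower the odds of entry in an arm, and *b* the factor by which they raise the odds of recurrence. Both effects are centred at the 30% prevalence:

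- entry odds, more treatments = p/(1−p) × a^(−0.7); fewer = p/(1−p) × a^(0.3)
- recurrence odds, more treatments = 0.18/0.82 × b^(0.7); fewer = 0.18/0.82 × b^(−0.3)
- share with more treatments in the subset = 0.3·e₁ / (0.3·e₁ + 0.7·e₀), where e₁ and e₀ are the entry probabilities
- subset recurrence = share × r₁ + (1 − share) × r₀

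Worked case, a = 3 in LLETZ only and b = 3:

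- LLETZ entry: e₁ = 0.441, e₀ = 0.703. Share = 0.3 × 0.441 / (0.3 × 0.441 + 0.7 × 0.703) = 0.212. In the imiquimod arm the share stays 0.300.
- Recurrence: r₁ = 0.3214, r₀ = 0.1364.
- LLETZ: 0.2119 × 0.3214 + 0.7881 × 0.1364 = 0.1756. Imiquimod: 0.3 × 0.3214 + 0.7 × 0.1364 = 0.1919.
- Odds ratio, imiquimod v LLETZ: (0.1919/0.8081) / (0.1756/0.8244) = 1.11, a difference of 1.6 percentage points with no true effect.

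The same formulas for other values:

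| a in LLETZ | a in imiquimod | b | Share LLETZ / imiquimod | Spurious odds ratio |
|---|---|---|---|---|
| 1 | 1 | 2 | 0.300 / 0.300 | 1.00 |
| 1.5 | 1.5 | 2 | 0.268 / 0.266 | 1.00 |
| 2 | 2 | 3 | 0.245 / 0.241 | 1.00 |
| 2 | 1 | 2 | 0.245 / 0.300 | 1.04 |
| 3 | 1 | 2 | 0.212 / 0.300 | 1.07 |
| 3 | 1 | 3 | 0.212 / 0.300 | 1.11 |
| 1 | 3 | 3 | 0.300 / 0.206 | 0.89 |

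A simulation of two million patients per row gave the same picture: 0.99 to 1.00 with equal selection, 1.04 to 1.11 with selection in LLETZ only, and 0.88 with selection in imiquimod only. By construction, the arm odds ratio within each treatment-history class is 1, so conditioning on the omitted term removes the bias in this illustration.

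**3. What the extra term costs.** The total of 433 less 20% loss leaves 433 × 0.8 = 346 patients. With (63% + 60%)/2 = 61.5% in the subset, 346 × 0.615 = 213. Background gives CIN 2–3 recurrence of 15–22% within 2 years: 213 × 0.15 = 32 and 213 × 0.22 = 47 events. Counting arm and each covariate as one parameter, events per parameter fall from 5.3–7.8 (six parameters) to 4.6–6.7 (seven). Recurrence in this plan is any abnormal cytology, a broader event than CIN 2–3, so these counts may be too low. Multi-category CIN grade or HPV subtype would use more parameters than counted here.

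**The case against.** Two outcomes may properly have two covariate lists. Nothing in the protocol says that they must match, and a reader who calls the difference a contradiction goes too far. This stands. What remains is that a factor named for one cytology outcome is dropped for a closely related one without a reason, in the analysis with less protection from randomisation.

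A reader might infer that the plan specifies a recurrence odds ratio by arm. It does not. The objective is worded as estimating a rate, and Statistical methods names no arm term. A comparison is only implied, because the model adjusts for covariates and both arms are followed. If no comparison is made, the bias described here does not arise.

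A reader might also infer that the dropped factor is a proven predictor of recurrence, or stronger than those retained. The documents show neither. Background cites another factor: "Margin involvement seemed to be a risk factor for developing residual or recurrent cervical dysplasia". The planning figures do suggest that treatment history matters, with about 90% success for surgical treatment in Background against 63% for a second LLETZ in Sample size calculation. They come from different sources and are not a like-for-like comparison.

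Finally, it is tempting to assume a large imbalance and report a large bias. Both arms are randomised ("Randomization is performed by use of a computerized randomization tool, to prevent selection and allocation bias"), so a systematic imbalance needs selection that differs by arm. Selection equal in both arms gives almost no bias. Very large imbalances would need strong selection in opposite directions, for which the documents give no ground.

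**Conclusion.** The point holds as a minor, cheaply corrected weakness of a secondary analysis. The omission is plain on the page and unexplained, and the analysis set is one in which randomisation does not guarantee balance on the omitted factor. Harm depends on three conditions: the model is used to compare arms; treatment history affects entry to the subset differently by arm; and treatment history predicts recurrence. The documents establish none of the three. Where all hold at the assumed strengths (odds ratios of 2 to 3), the spurious odds ratio runs from about 0.89 to 1.11 and can favour either arm.

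Two stronger conclusions are not supported. The primary non-inferiority result is not affected, since it rests on a separate analysis by intention to treat. Nor would the added covariate make the recurrence comparison unbiased, because selection into the subset can act through other factors that the model does not contain.

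**What to change.** In Statistical methods, add number of previous treatments to the covariates of the recurrence model. The regression analysis already needs this variable, so it has to be available even though the baseline list shows only medical history and not the count itself.

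The cost is one more parameter (if coded in two classes) in a secondary model with limited events, roughly one event per parameter fewer on the figures above. Sexual behaviour would still appear in the recurrence model only, so the lists would not become identical; a short reason for that difference would be enough. The change does not deal with selection into the adequately treated subset, which is a separate limitation to keep in mind when the results are read.
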